### Measures taken to minimize/avoid bias

#### Randomization

The internet-based randomization will be conducted according to a central computerized randomization schedule, with a 1:1 treatment allocation ratio, stratified by centre, in blocks of variable size, to guarantee concealment. No-one can delete records from the randomization database, so that all randomizations have to be accounted for. Audit log files detailing all activity on the randomization system are available to the trial coordinator.

#### Blinding

All clinical ratings will be completed by trained and independent evaluators blinded to treatment assignment. Each of the sites implements procedures to mask a patient treatment assignment from the person who will evaluate the results of the clinical ratings through the following: 1) locating the rater at a separate physical location, and 2) reminding the patients at each visit not to mention anything that might reveal their treatment condition to the independent evaluator. The baseline and the HRSD interview at 20 weeks are videotaped and will be evaluated by another rater.

#### Control of therapy allegiance

Several recommendations for how to minimize the allegiance effect are considered: involving several investigators who represent a "mix of therapy allegiances", comparing interventions of the same length and duration, using blinded raters for process and outcome analyses, and conducting both interventions in all sites [53].

#### Control for overlapping treatments

The following measures are taken to prevent confounding of treatment conditions through the overlap of treatment methods:

Each therapist will conduct only one of the two treatments. The therapists are obligated to adhere to the therapeutic procedures and interventions described within the manuals. Adherence to the treatment manuals will be continuously supervised by rating videotapes of the sessions on a randomized basis using adherence scales [19,29]. The validity of the therapist's statements will be checked through external assessment of the video recordings. In the post-hoc-analysis it will be checked if the expected differences regarding intervention characteristics appear within the therapies.

#### Control for confounding factors

The influence of the trial site upon the effectiveness of the respective treatment approaches will be investigated as a separate factor. In addition, patients are asked not to engage in off-study psychosocial (e.g., group therapy) or psychiatric interventions (e.g. antidepressive medication) during the treatment period.

### Statistical methods

#### Power calculation

The sample size calculation is based on the primary hypothesis testing CPASP against SP with regard to mean HRSD-scores at the end of the acute treatment phase (null hypothesis: identical expected HRSD). We considered a difference of five points on the HRSD between mean post-treatment scores after 24 sessions of the treated groups as clinically relevant. In similar studies, standard deviations of post-intervention HRSD-scores of groups receiving CBASP, SP, or combinations range from 5.4 to 10.4 points [12,16]. Assuming a common standard deviation of 10 points for two-group comparisons yields a medium-sized effect of 0.5 (Cohen's d). To detect this effect by a two-tailed t-test with a power (1-β) of 0.95 and type I error probability level of α = 0.05 for significance, 210 patients (105 per group) are needed.

Assuming a drop-out rate of approximately 20% from baseline to week 20, the maximum sample size is fixed as 268 patients to be randomized. This is the number needed for an appropriately powered per-protocol analysis (only completers are analyzed). In the intention-to-treat analysis, the higher number of patients is expected to be compensated by a potential dilution of treatment effects, so that the power will be approximately the same.

#### Analyses

The final analyses will be performed in the intention to treat (ITT) population, analyzing patients in treatment groups to which they were randomized, and using the last observation carried forward (LOCF) method in case of missing outcome data at week 20. Because of the chronic nature of the disorder, spontaneous remission is unlikely to happen.

At main analysis, the null hypothesis of equal efficacy will be tested (two-sided test) using analysis of covariance (ANCOVA) controlled for pre-treatment scores and site. Secondary analyses of the primary endpoint will include a per-protocol approach, regression controlling for additional factors, and exploratory analyses of treatment effect modifiers. To examine changes over time, a mixed model approach to repeated measures with 2 treatments by 4 measurement points will be used: baseline, after 12 weeks, after 20 weeks (acute intervention), and after 28 further weeks of continuation treatment. Analyses of continuous secondary variables will be performed using linear mixed models. For remission rates, chi-squared tests and logistic regression will be used. The analysis of time to remission and time to response will be analyzed using standard survival analysis techniques. Level of significance will be set at α = .05

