### Endpoints

#### Primary endpoint

Depressive symptoms 20 weeks after randomization (after acute treatment phase) as measured by the 24-item HRSD.

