#### Secondary endpoints

Among others:

a) Depressive symptoms after 12 and 48 weeks measured by the HRSD;

b) Remission rates after 12, 20, and 48 weeks utilizing the IDS-SR and defining remission a priori as a score of 13 or less for at least three consecutive weeks.

c) HRSD-remission rates (HRSD ≤ 8) and HRSD-response rates (HRSD score by at least 50 percent from baseline) will be calculated for the main measurement time points.

d) Changes in *QIDS-C16 *(from baseline to week 12, 20, and 48);

e) Temporal changes in *IDS-SR *- Total sum score between baseline assessment and follow-up assessments (time course of 27 time points).

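### LOCF for missing week-20 HRSD makes the primary ANCOVA sensitive to unequal drop-out between arms, and the stated rationale does not cover this

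*Protocol article*

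**What the plan says.** The primary endpoint is "Depressive symptoms 20 weeks after randomization (after acute treatment phase) as measured by the 24-item HRSD". Under Analyses it is tested two-sided by ANCOVA, adjusted for the pre-treatment score and site, in the ITT population, "using the last observation carried forward (LOCF) method in case of missing outcome data at week 20". The next sentence is the only justification: "Because of the chronic nature of the disorder, spontaneous remission is unlikely to happen".

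The HRSD occasions can be read from two places. Secondary endpoints lists "Depressive symptoms after 12 and 48 weeks measured by the HRSD", and Analyses sets out "2 treatments by 4 measurement points will be used: baseline, after 12 weeks, after 20 weeks (acute intervention" and then the end of the 28 continuation weeks. The denser series, "time course of 27 time points", belongs to the self-rated IDS-SR, not to the HRSD.

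The Power calculation section plans as follows: "Assuming a drop-out rate of approximately 20% from baseline to week 20". It gives no figure by arm. It also expects the ITT contrast to be weakened somewhat, and the larger number of patients to make up for this, so that power stays about the same.

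**The concern.** If the text names every HRSD rating, a patient lost before week 12 enters the primary analysis with the entry score, and a patient lost later enters with a mid-treatment score. By week 12 the schedule has delivered 16 sessions (two a week for 4 weeks, then one a week for 8). The remark on spontaneous remission concerns untreated change. It does not address change brought about by therapy after the carried rating, nor the case where one arm loses more patients than the other.

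Both arms receive an active therapy, so improvement is expected in both. Each carried score then leaves out part of that improvement, and the arm with more drop-outs looks worse for that reason alone. A larger sample does not remove this error. Single imputation also treats carried values as if they had been observed. The test affected is the trial's one confirmatory comparison.

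**Working it through.** **The plan's own figures.** A difference of 5, SD 10, two-sided α 0.05 and power 0.95 give 105 per group by the noncentral t (power 0.9501), as stated. Allowing for 20% drop-out, 210/0.80 = 262.5, so 263. The stated 268 corresponds to 1 − 210/268 = 21.6%, which fits approximately 20%. The sample size is not in question. With 134 per arm and no missing data, unadjusted power for 5 points would be 0.983.

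**Notation.**
- d: proportion missing at week 20 in an arm.
- q: share of those patients who have a week-12 score.
- f: share of the week-20 improvement present by week 12.
- A carried score misses on average (1 − q·f) of the arm's improvement.

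**Assumptions not in the document.**
- Baseline mean 27 and SD 5; week-12 SD 9.
- Correlations 0.4 (baseline with later scores) and 0.7 (week 12 with week 20).
- SP improvement of 6, 10 or 14 points.
- f = 0.6 in the simulations, 0.4 to 0.8 in the equal drop-out formula.
- Drop-out unrelated to outcome within arm; no site effect.
- The week-20 SD of 10 is the plan's.

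**Equal drop-out of 20%, true difference 5.** Expected estimate = 5 × (0.80 + 0.20·q·f).
- q = 0: 5 × 0.80 = 4.0, unadjusted power 0.904.
- q = 0.5, f = 0.6: 5 × 0.86 = 4.3, power 0.939.
- q = 1, f = 0.8: 5 × 0.96 = 4.8, power 0.975.

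With no true effect, simulated type I error was 4.8% to 5.4%.

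**Unequal drop-out, no true effect.** False difference ≈ (drop-out gap) × (improvement) × (1 − q·f). For 15% CBASP vs 25% SP, with 134 per arm and baseline-adjusted ANCOVA:

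| Improvement | q | Formula | Simulated | Type I error |
|---|---|---|---|---|
| 6 | 0 | 0.10 × 6 = 0.60 | 0.61 | 8.6% |
| 6 | 0.5 | 0.10 × 6 × 0.7 = 0.42 | 0.43 | 6.6% |
| 10 | 0 | 0.10 × 10 = 1.00 | 1.03 | 15.3% |
| 10 | 0.5 | 0.10 × 10 × 0.7 = 0.70 | 0.69 | 9.6% |
| 14 | 0 | 0.10 × 14 = 1.40 | 1.42 | 21.4% |
| 14 | 0.5 | 0.10 × 14 × 0.7 = 0.98 | 0.96 | 13.0% |

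If every drop-out had a week-12 score (q = 1, not simulated under no effect), the formula gives less: 0.10 × 6 × 0.4 = 0.24 to 0.10 × 14 × 0.4 = 0.56 points.

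**Unequal drop-out, true difference 5.** Estimate ≈ (I + 5)·[1 − d_CBASP·(1 − q·f)] − I·[1 − d_SP·(1 − q·f)], where I is the SP improvement (6 or 10 points here).
- 25% CBASP vs 15% SP, I = 10, q = 0: 15 × 0.75 − 10 × 0.85 = 2.75 (simulated 2.76, power 0.64).
- Same drop-out, I = 6, q = 1: 11 × 0.90 − 6 × 0.94 = 4.26 (simulated 4.27, power 0.97).
- 15% CBASP vs 25% SP, I = 10, q = 0: 15 × 0.85 − 10 × 0.75 = 5.25 (simulated 5.22). All such cases gave 4.9 to 5.2, so dilution and bias roughly cancel.

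**Is LOCF the cause?** In a separate scenario (means 27/20/17, SDs 5/8.5/10, 60% of drop-outs leaving before week 12), LOCF at 15% vs 25% and no effect gave 0.7 to 0.8 points and a type I error of about 10%. A baseline-adjusted analysis of observed week-20 scores under the same assumptions stayed near 5% type I error and, with a true effect, near 5.0 points. The mixed model itself was not simulated.

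**The case against.** The strongest defence is that LOCF suits this population. These are unmedicated patients with a chronic disorder. If someone leaves therapy and then stays at the last rated level, the carried score is right, a difference in retention is a real difference in outcome, and a missing-at-random model would miss it. This stands as a possibility, and it is why any replacement needs a sensitivity analysis of its own. It does not rescue a baseline score carried for a patient who had several weeks of therapy after that rating.

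Other points also stand:
- The arms are matched for session number, duration and therapist experience, and nothing in the document says that drop-out will differ.
- The 20% is a drop-out allowance for the completer analysis. Patients who stop therapy may still be rated, so missingness may be lower.
- The design figure was not available for this check, so a further or early-termination HRSD rating cannot be ruled out. The text names none.
- The protocol foresees dilution. Its view that power stays about the same is roughly borne out, unless nearly all drop-outs carry baseline scores.

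A reader might infer that the primary and mixed-model analyses conflict. They do not: the ANCOVA is named as the main analysis and the mixed model is for change over time. Nor is the absence of a stated sensitivity analysis for missing data a fault in itself, since that may stand in an analysis plan that is not shown.

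**Conclusion.** The point holds in conditional form. The protocol fixes LOCF for its confirmatory test and supports it with a reason that covers neither change during therapy after the carried rating nor unequal drop-out.

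Two stronger readings are not supported. One is that type I error is uncontrolled in general: at equal drop-out it stays near 5%, and inflation needs a gap between arms that the document neither states nor excludes. The other is that LOCF always dilutes: it does so at equal drop-out or when CBASP loses more patients, but not when SP loses more.

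At a 10-percentage-point gap the distortion is material against a 5-point target. It ranges from a false difference of about 0.4-1.4 points (type I error about 7-21%) to a true effect estimated at about 2.8-4.3 points. The direction is clear once a gap and general improvement are assumed. The size depends on assumed means, SDs, correlations, timing and drop-out by arm, and on drop-outs otherwise following the course of those who stayed.

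**What to change.** Before unblinding, change the primary analysis in one of two ways.
- Use the week-20 treatment contrast from the model already planned ("a mixed model approach to repeated measures with 2 treatments by 4 measurement points will be used"), with treatment by visit, all observed HRSD scores, and adjustment for baseline HRSD and site. The planning sentence does not name the scale, so state that it is the HRSD.
- Or keep the ANCOVA, applied after multiple imputation by arm, with week-12 HRSD and the serial IDS-SR scores as auxiliary variables.

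Keep LOCF as a sensitivity analysis. Add a delta-adjusted analysis, because both options assume data missing at random and drop-outs may do worse than that assumption implies.

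The cost is wording only, with no new data and no more patients. The downside is that the primary result then rests on the missing-at-random assumption, and its interval will reflect the missing data.

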## Objectives

The purpose of the study is to estimate the efficacy of CBASP compared to non-specific supportive psychotherapy (SP) in 268 medication free, early onset chronically depressed outpatients. The primary hypothesis is that CBASP is more effective in reducing depressive symptoms than SP. The secondary hypothesis assumes that the remission rates are higher in CBASP compared to SP.

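### At week 20, LOCF can complete the three-week IDS-SR remission run with scores nobody observed, and excluding remission from LOCF leaves an analysis of known cases only

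*Protocol article*

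**What the plan says.** The Objectives section of the protocol article makes remission the secondary hypothesis: "The secondary hypothesis assumes that the remission rates are higher in CBASP compared to SP".

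Under Secondary endpoints, item (b) is "Remission rates after 12, 20, and 48 weeks utilizing the IDS-SR", "defining remission a priori as a score of 13 or less for at least three consecutive weeks". Item (c) adds a second remission definition based on a single HRSD score of 8 or below. Item (e) describes the IDS-SR as a "time course of 27 time points".

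The Analyses section sets the population: "The final analyses will be performed in the intention to treat (ITT) population, analyzing patients in treatment groups to which they were randomized". The same sentence gives the article's only missing-data rule: "using the last observation carried forward (LOCF) method in case of missing outcome data at week 20". Neither part is limited to the HRSD or to the primary endpoint. For the binary outcome the section says: "For remission rates, chi-squared tests and logistic regression will be used". It also plans survival methods for time to remission, and linear mixed models for the continuous secondary variables.

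**The concern.** The sustained definition exists so that one low score does not count as remission. LOCF repeats one observation. Applied to IDS-SR scores, it can turn a single last score of 13 or less into a run that was never seen, which is exactly what the definition is meant to rule out. The article supports LOCF by noting that patients with a chronic disorder rarely remit spontaneously. That is an argument for carrying a high score forward, not a low one.

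The other reading is that LOCF was meant only for the HRSD. Neither a chi-squared test nor a logistic regression can then use a patient whose remission status is unknown. The week-20 comparison would cover only patients with known status, although the sentence promises all patients as randomised. Continuous outcomes have mixed models that use partial follow-up; the remission rates have no equivalent.

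At stake is the week-20 rate for the first remission endpoint listed, which bears directly on the secondary hypothesis.

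**Working it through.** **1. The plan's own figures (Power calculation).** A difference of 5 points, SD 10, two-sided α 0.05 and power 0.95 give 104.93 per group by the exact t-test, so 105 per group and 210 in total (power 0.950). This reproduces the stated 210. For dropout, 210 / (1 − 0.20) = 262.5, so 263; the stated 268 implies 1 − 210/268 = 21.6%, consistent with a rate given as approximate. The article gives no figure for remission.

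**2. What score-level LOCF does to a dropout before week 20.**
- Last score above 13: carried forward as a non-remitter.
- Last score 13 or less, run already complete: the remission was observed.
- Last score 13 or less, run not complete: LOCF supplies the missing weeks and creates a remitter. Only this group is at issue.

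**3. Effect on one arm's rate.** Inputs: 268 randomised 1:1, so 134 per arm; dropout d = 0.20, so 0.20 × 134 = 26.8, about 27 patients. Let q be the share of dropouts in the third group (not given; assumed). The addition to the arm's rate is d × q. For q = 0.10 this is 0.20 × 0.10 = 0.02, or 2 percentage points (26.8 × 0.10 = 2.7 patients). Over both arms (53.6 dropouts), q of 0%, 10%, 30% and 100% adds about 0, 5, 16 and 54 remitters, that is 0, 2, 6 and 20 points on the pooled rate. The last is a mathematical limit, not an expectation.

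**4. Effect on the difference.** Arm rate = (1 − d)·p + d·q, with p the remission rate in completers. Illustration with assumed p of 30% (CBASP) and 20% (SP), and the same q in both arms:

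| Dropout CBASP / SP | Completers only | Dropouts not remitted (q = 0) | LOCF, q = 30% |
|---|---|---|---|
| 20% / 20% | 10.0 | 24.0 − 16.0 = 8.0 | 30.0 − 22.0 = 8.0 |
| 15% / 25% | 10.0 | 25.5 − 15.0 = 10.5 | 30.0 − 22.5 = 7.5 |
| 25% / 15% | 10.0 | 22.5 − 17.0 = 5.5 | 30.0 − 21.5 = 8.5 |

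The false carry-in shifts the difference by d₁q₁ − d₂q₂. This is zero when dropout and q are equal in both arms (first row), and it can go either way otherwise.

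**5. The completer reading.** Assume dropout of 15% and 25%, remission of 40% in completers of both arms and 10% in dropouts. The test compares 40% with 40%. In all randomised patients the rates are 0.85 × 40 + 0.15 × 10 = 35.5% and 0.75 × 40 + 0.25 × 10 = 32.5%, a difference of 3.0 points.

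**6. The schedule.** Weekly scores over 48 weeks need at least 48 time points; the article gives 27. If, as an assumption, scoring were weekly from baseline to week 20 (21 points), 6 points would remain for the next 28 weeks. Three successive scores need not then be three successive weeks, even without dropout.

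**The case against.** Read literally, the rule fills a value missing at week 20, which is the HRSD time point, and the ANCOVA follows directly. It does not say that earlier missing IDS-SR weeks are filled, and it could be read as carrying remission status forward, which would create no false runs. This stands as a possible reading. The text does not choose it, however, and its wording covers the final analyses without exempting remission.

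A condensed article may leave the handling of a missing binary endpoint to the full protocol or analysis plan. That disposes of any complaint about silence at weeks 12 and 48. It does not dispose of the week-20 point, which rests on a rule the article states.

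A reader might infer three stronger things that the article does not support:
- That every dropout is either turned into a remitter or dropped. Under LOCF, those last seen above 13 become non-remitters, and nowhere does the article say that dropouts are excluded.
- That remission rests on a chi-squared test alone. Logistic regression is also planned, and survival analysis can censor dropouts. The first does not solve missing outcomes, and the second does not give week-20 rates, but both belong in the picture. The HRSD remission endpoint uses a single score and is free of the run problem, and the secondary hypothesis does not say which definition it means.
- That the treatment comparison is shown to be biased. It is not: carry-in cancels if the arms behave alike. The 3.0 points in the completer example rest on assumed inputs and compare with a standard error of about 5.8 points, √(2 × 0.34 × 0.66 / 134).

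**Conclusion.** The point holds for IDS-SR remission at week 20. The stated LOCF rule, applied to scores, defeats the sustained definition for patients who leave on a low score with the run incomplete. Leaving remission outside the rule gives an analysis of known cases that conflicts with the stated population. The documented quantity is the planned dropout of about 20%; the 2 points per 10% of dropouts follows from it by arithmetic. The share carried in, dropout by arm and the remission rates are all assumptions, so neither the size nor the direction of any error in the treatment difference can be computed. The illustrations show only that the choice of handling can matter: from 5.5 to 10.0 points in the least favourable row.

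**What to change.** For week-20 IDS-SR remission:
- State that carried-forward scores do not count towards the three-week run.
- Replace LOCF with multiple imputation of the IDS-SR course in all randomised patients, using arm, site, baseline and observed scores. Derive remission in each imputed set and combine the results.
- Count missing as not remitted in a sensitivity analysis.
- Wherever the IDS-SR is not scheduled weekly, say how the three-week criterion is judged from the 27 time points.

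The cost is analysis-plan wording and an imputation step; no new data are collected. The downside is more programming and a missing-at-random assumption, against which the sensitivity analysis gives a simple, conservative rate for each arm, though not necessarily a conservative difference.

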## Discussion

Specific and effective treatment strategies for chronic depression are urgently needed since the disorder is not only recognized as highly prevalent and particularly impairing, but is also considered "difficult-to-treat" or even treatment resistant by most clinicians. There are only a few studies on chronic depression indicating that traditional interventions are less effective than in acute, episodic depression. In addition, most of the studies had methodological weaknesses, such as the very short courses of psychotherapy. Usually, chronic depression begins early in life, is often associated with early interpersonal trauma, and the early onset course results in an even more substantial human capital loss than the late-onset. Furthermore, early onset depression shows a weak response to medication and a high rate of relapse after an initial response. Innovative antidepressant approaches should aim at the regulation and maintenance of mood stability over the long term rather than at the acute resolution of symptoms. The only specific and promising psychological intervention for chronic depression, the CBASP, focuses on the patient's central mechanisms of derailed affective and motivational regulation by using the therapeutic relationship in a personal, disciplined way to shape dysfunctional interpersonal behaviour. With the present multisite study, the efficacy of CBASP is compared with a non-specific supportive psychotherapy (a well-designed psychological control treatment) in early onset chronically depressed patients. The CBASP approach faired very well in one large trial but has never been directly compared to a non-specific control as first-line treatment. Another innovative aspect of the study is the use of an extended course of psychotherapy (32 sessions) since the very short courses of psychotherapy in the study by Keller et al. [12] and in other trials on chronic depression were probably too short to provide an adequate test of psychotherapy. Furthermore, it is planned to identify predictors of response to CBASP vs. SP (e.g. early childhood trauma). In process research, we will investigate which elements of psychotherapy are most critical for an antidepressant response to further improve the approach, if indicated.

